### 2.3. Randomization and Blinding

Patients will be randomly allocated to either the experimental group (QDP; approximately n = 50) or the control group (CDC; approximately n = 50). Stratified randomization will be based on age and will be carried out by a researcher not directly involved in the study. The patients will be unaware of whether they belong to the experimental or the control group. The researchers and laboratory personnel who will be involved in data collection and measurements (excluding the researcher who will be involved in dietetic counseling) will not know if a participant is included in the QDP group or the CDC group. The study is designed as a single-blinded study without a placebo.

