### 2.11. Sample Size

The minimum sample size was calculated based on the expected improvement in overall QoL (decrease in points) and BMI (decrease in kg/m^2^) after the six-month follow-up and the expected difference between the experimental and the control group. A decrease in overall QoL and BMI with a 50% difference between groups (in the experimental/control group, a decrease by 20/10 points and 2.0/1.0 kg/m^2^, respectively) was assumed. For this calculation, a 5% significance level and 80% power were considered. The sample size required at baseline is approximately 100 respondents (for the experimental/control group: 50/50 for overall QoL and 42/42 for BMI), including a 20% drop-out rate at the end of the study. When the data collection is completed, the adequacy of the study sample will be checked by applying the post hoc statistics to calculate power.

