### 2.12. Statistical Analysis

Categorical variables will be presented as a sample percentage (%) and continuous variables will be presented as means with a 95% confidence interval (95%CI) or medians with an interquartile range (IQR) for variables with normal or non-normal distribution, respectively. To assess the impact of dietetic counseling and verify the differences between the experimental and the control group, two-tailed tests will be applied; *p*-values < 0.05 will be considered significant. 

The normality of variable distribution will be verified with a Kolmogorov–Smirnov test before the statistical analysis. For continuous variables, e.g., diet quality scores, AdhS, scores of QoL, nutrition knowledge score, TFTs, markers of adiposity, metabolic parameters, and changes after a six-month follow-up with respect to baseline will be verified with a T-test for dependent samples or a Mann–Whitney test, for variables with normal or non-normal distribution, respectively. For categorical variables, logistic regression modeling will be applied to determine the chance of the occurrence of high diet quality, high AdhS, high QoL, as well as low adiposity and elevated metabolic parameters. The odds ratios (ORs) and 95% confidence intervals (CIs) will be calculated. The significance of ORs will be verified with Wald’s statistics. A crude model and models with an adjustment for confounders will be created. All analyses will be performed with Statistica software (version 13.3 PL; StatSoft Inc., Tulsa, OK, USA; StatSoft, Krakow, Poland).

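### Continuous outcomes measured at baseline and six months in both arms are tested without their baseline value or age, losing precision that is free to recover, though little where the two measurements correlate highly

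*Protocol article*

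**What the plan says.** Section 2.12 sets its tests the task to "verify the differences between the experimental and the control group, two-tailed tests will be applied". The outcomes are listed as "For continuous variables, e.g., diet quality scores, AdhS, scores of QoL, nutrition knowledge score, TFTs, markers of adiposity, metabolic parameters", followed by "changes after a six-month follow-up with respect to baseline", to be tested with a dependent-samples t-test or a Mann–Whitney test, the choice depending on normality.

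The only mention of adjustment is "A crude model and models with an adjustment for confounders will be created". It comes after the logistic regression, odds-ratio and Wald sentences for categorical outcomes, and it names no confounders.

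Elsewhere in the article:
- Section 2.3: "Stratified randomization will be based on age". No other stratification factor is given, and the age bands are not defined.
- Table 1: diet quality, quality of life, nutrition knowledge, adiposity, metabolic parameters and thyroid function are collected at T1 and at T3 in both arms.
- Sections 1.2 and 2.4: the adherence score (AdhS) comes from diaries that only the experimental group keeps, during the six months.
- Section 2.11: the baseline size per arm is "50/50 for overall QoL and 42/42 for BMI", including 20% drop-out.

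**The concern.** The trial's question is whether QDP does better than CDC. With about 40 completers per arm, the arms can differ by chance at T1 on any outcome, since only age is balanced by design. A raw change score subtracts the whole T1 value, which fixes its slope at 1. When the T1–T3 correlation is below 1, that is too much, so an arm that happens to start worse appears to improve more. The change score also carries more variance than an analysis that estimates the slope. The T1 value is already collected for these outcomes, so the loss is avoidable at no cost in data.

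This is separate from the choice between a paired and an unpaired test. A correct unpaired test on raw change would still carry the loss.

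**Working it through.** **Inputs.** From section 2.11: between-arm differences of 20 − 10 = 10 points (overall quality of life) and 2.0 − 1.0 = 1.0 kg/m² (BMI), "a 5% significance level and 80% power were considered", and 20% drop-out. Tests are two-sided (section 2.12). Assumed because the article does not give them: r, the T1–T3 correlation of an outcome; equal SDs at T1 and T3; and a two-sample test on change as the reference.

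**The plan's own sample size.** No SD is stated, so the size cannot be reproduced forward. Solving backward with SD = difference / [(1.960 + 0.842) × √(2/n)]:
- Quality of life: 50 × 0.8 = 40 completers per arm; SD of change = 10 / (2.802 × 0.2236) = 15.96 points. An exact t calculation gives 15.8. If drop-out was added as n × 1.2 instead, completers are 41.67 and the SD is 16.3.
- BMI: 42 × 0.8 = 33.6 completers per arm; SD of change = 1.46 kg/m².

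Forward check for quality of life: an SD of 16 needs 41 completers per arm, which is 52 at baseline by 41/0.8 or 50 by 41 × 1.2. The stated size is attainable but cannot be verified.

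**Variance.** With a common SD σ, raw change has variance 2σ²(1 − r) and the T1-adjusted analysis σ²(1 − r²). The ratio of adjusted to raw is (1 + r)/2.

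**Adjusted power.** Φ(2.802/√((1+r)/2) − 1.960). At r=0.5: 2.802/0.866 − 1.960 = 1.275, giving 89.9%.

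**Shift from chance imbalance.** Given a T1 difference D between arms, the raw-change contrast moves by (1 − r)D in size. The baseline SD is 15.96/√(2(1 − r)), and one standard error of D is that SD × √(2/40). At r=0.5: the SD is 15.96, D = 3.57 and the shift is 1.78 points.

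Quality of life, 40 completers per arm, 80% power for raw change:

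| r | (1+r)/2 | Adjusted power | Completers per arm for 80% if adjusted | Baseline SD | One-SE imbalance | Shift (points) |
|---|---|---|---|---|---|---|
| 0.3 | 0.65 | 93.5% | 26 | 13.5 | 3.02 | 2.11 |
| 0.5 | 0.75 | 89.9% | 30 | 16.0 | 3.57 | 1.78 |
| 0.7 | 0.85 | 86.0% | 34 | 20.6 | 4.61 | 1.38 |
| 0.9 | 0.95 | 82.0% | 38 | 35.7 | 7.98 | 0.80 |
| 0.95 | 0.975 | 81.0% | 39 | 50.5 | 11.29 | 0.56 |

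At r=0.5, adjustment is worth 40/0.75 ≈ 53 completers per arm analysed by raw change. The r=0.95 row is only a limit: if overall quality of life is scored 0 to 100 like the 13 scales in section 2.7, an SD of 50.5 exceeds half the range and is not possible.

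**BMI.** Taking 33 completers per arm for 80% power on raw change, adjustment needs 30 at r=0.8, 32 at r=0.9 and 33 at r=0.95. The implied baseline SD is 1.46/√0.2 ≈ 3.3 kg/m² at r=0.9 and 1.46/√0.1 ≈ 4.6 at r=0.95. Both fit the eligible range of 18.5 to below 35 in Table 2, so a high r, and hence almost no gain, is credible for BMI.

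**The case against.** **The reference analysis is not the one written.** For normally distributed variables section 2.12 names a within-arm test, which yields no QDP-versus-CDC effect at all; Mann–Whitney is the only between-arm test named for continuous data. The figures above therefore describe a corrected plan, not either named test. This stands. The dependent-samples test is the more serious defect in that sentence and must be repaired first. It does not remove the point, because the obvious repair, an unpaired test on change, would keep the loss.

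**Scope.** A reader might infer that every continuous outcome is affected. The documents do not support that. AdhS is in the list but has no T1 value and no control-arm value, and the sentence lists the variables themselves beside their changes.

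**Bias.** A reader might infer that the planned effect estimate would be biased. It would not be: over randomisations, a between-arm comparison of change is unbiased. The shifts in the table are conditional on an imbalance of that size occurring.

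**Size.** A reader might take the r=0.5 figures as the expected loss. The article gives no r, and at r=0.9 power rises only from 80% to 82%. The SD is back-solved as well. No magnitude can be given for leaving out age.

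**Left to an analysis plan.** Covariates are often specified there, and none is shown. Silence would be no fault, but the article is not silent: it names tests that cannot take a covariate and mentions adjustment only after the logistic models.

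**Conclusion.** For the continuous outcomes measured at T1 and T3 in both arms, the stated methods leave the T1 value and age out of any between-arm comparison. Adjustment would reduce the variance of that comparison by (1 − r)/2: 35% at r=0.3, 25% at r=0.5, 15% at r=0.7, 5% at r=0.9 and 2.5% at r=0.95. For quality of life, which sets the sample size, the gain is material if r is about 0.3 to 0.7. For BMI it may be negligible. At high r the adjusted analysis still loses essentially nothing, one degree of freedom for the T1 term.

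This rests on equal T1 and T3 SDs, a two-sample test on change as the reference, and 40 completers per arm with 80% power for raw change. An unadjusted between-arm comparison of change would be valid, so this is an inexpensive improvement in precision and not a correction of an invalid analysis.

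**What to change.** In section 2.12, for each continuous outcome measured at T1 and T3 in both arms:
- Fit a linear model of the T3 value on arm, the T1 value of the same outcome and age (the stratification factor). Where the outcome is markedly non-normal, use a transformed scale or a rank-based equivalent.
- Report the adjusted QDP − CDC difference with its 95% CI as the treatment effect.
- Keep within-arm paired tests and raw change as description.

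In the adjusted logistic models, include T1 status and age wherever the outcome is measured at T1. Report AdhS for the QDP arm only.

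The same change supplies the between-arm test that is missing for normally distributed variables. It costs a rewording of section 2.12 and a statement of how age enters the model, since section 2.3 does not define the strata. It needs no further patients, visits or measurements.

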### 2.5. Diet Quality 

To collect dietary data, the semi-quantitative food frequency method will be applied, and a food frequency questionnaire (KomPAN) will be used. The KomPAN questionnaire consists of 46 food items and includes a comprehensive variety of foods usually consumed in Poland [30]. The KomPAN questionnaire has been assessed in healthy/unhealthy subjects as reliable tools with acceptable to very good reproducibility [30,31]. To assess diet quality, two predefined diet quality scores (the a priori approach) will be used: pro-Healthy-Diet-Index (pHDI) and non-Healthy-Diet-Index (nHDI).

Participants will be asked to indicate the average frequency of consumption of each food item over the 12 last months. Enrolled participants will receive a questionnaire from trained researchers, who will provide guidance and assistance as required on a one-to-one basis. 

To indicate food frequency consumption, respondents will choose one of six categories (converted into daily frequency): ‘never’ (0 times/day), ‘1–3 times a month’ (0.06 times/day), ‘once a week’ (0.14 times/day), ‘few times a week’ (0.5 times/day), ‘once a day’ (1.0 time/day), or ‘few times a day’ (2.0 times/day) [31]. Daily frequencies of 24 food items will be used to calculate pHDI and nHDI. The pHDI includes 10 food items: wholemeal bread/bread rolls, coarse-ground groats, milk, fermented milk drinks, cheese curd products, white meat, fish, legumes, fruit, and vegetables. The nHDI includes 14 food items: white bread and bakery products, white rice and fine-ground groats, fast foods, fried foods, butter, lard, cheese, cured meat/smoked sausages/hot dogs, red meat, sweets, tinned meats, sweetened carbonated or still drinks, energy drinks, and alcoholic beverages. Daily frequencies of the consumption of the selected 10 (pHDI) or 14 (nHDI) food items will be summed up and recalculated into a range of 0%–100% points according to the questionnaire’s manual [30]. A higher percentage of points reflected greater adherence to the diet quality score, i.e., for pHDI – better diet quality and for nHDI – worse diet quality.

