### 2.7. Quality of Life (QoL) 

To assess QoL, a thyroid-specific questionnaire (ThyPRO) in a Polish version (ThyPROpl) will be applied [32]. There is substantial evidence for the clinical validity and reliability of the questionnaire in patients with mild thyroid disorders [33,34]. The ThyPRO consists of 84 items summarized in 13 scales as well as a single item measuring the overall impact of thyroid disease on QoL within the last four weeks. The questionnaire covers physical symptoms specifically relevant to thyroid diseases (e.g., symptoms of hyperthyroidism and goitre) and non-specific aspects of high importance to patients with thyroid diseases (e.g., fatigue). Responses for each item will be scored with points on a five-point Likert scale as follows: ‘not at all’ (0 points), ‘a little’ (1 point), ‘some’ (2 points), ‘quite a bit’ (3 points), and ‘very much’ (4 points). The average score of items in a scale will be divided by four and multiplied by 100 to yield 13 scales ranging from 0 to 100 points [32,33], with higher point scores indicating a worse quality of life related to each scale.

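### The only comparative effect measure with a confidence interval is an odds ratio, which for QoL and diet quality rests on cut-up 0–100 scores, while the trial is sized on a continuous between-arm difference that gets no named estimate

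*Protocol article*

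**What the plan says.** **What the trial is sized on.** Protocol article, section 2.11, assumes "in the experimental/control group, a decrease by 20/10 points and 2.0/1.0 kg/m^2^, respectively", so the between-arm differences are 10 QoL points and 1.0 kg/m². On error rates it says "For this calculation, a 5% significance level and 80% power were considered". The resulting numbers are "50/50 for overall QoL and 42/42 for BMI" at baseline, with a 20% drop-out allowance included.

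**How the outcomes are scored.** Section 2.7 puts each ThyPRO scale on 0–100, "with higher point scores indicating a worse quality of life related to each scale". Section 2.5 puts pHDI and nHDI on 0–100%: "A higher percentage of points reflected greater adherence to the diet quality score". For nHDI that means a worse diet. Neither section gives a boundary for a high category. The article does give boundaries for the adherence score (section 2.4), adiposity (2.9) and metabolic markers (2.10).

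**How the outcomes are analysed.** Section 2.12 says that "two-tailed tests will be applied". It describes continuous variables by means with 95% CI or medians with interquartile range. It tests them, including QoL scores, diet quality scores and six-month changes, by a dependent-samples t-test or a Mann–Whitney test. It then states that "logistic regression modeling will be applied to determine the chance of the occurrence of high diet quality, high AdhS, high QoL", together with adiposity and metabolic categories. Odds ratios with 95% CI, Wald tests, and crude and adjusted models belong to this second part only.

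**The concern.** The sample size and the effect estimates do not describe the same quantity. A reader who wants to know whether QDP beats CDC by the planned 10 QoL points or 1.0 kg/m² is promised summaries and p-values for the continuous scores, and a comparative estimate with an interval only for high versus not high. The only covariate-adjusted comparison is also on the cut outcomes.

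Cutting a 0–100 score treats a woman just above the boundary as different from one just below it, and as the same as one far above it. That discards information, so the odds ratio has a wide interval and less power than the uncut score. Its size also depends on where the boundary lies. A non-significant odds ratio for high QoL could be read as no benefit although the planned effect was present, and no between-arm interval is promised against which to check that reading.

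**Working it through.** **Inputs**
- Two-sided 5% and 80% power: sections 2.12 and 2.11.
- QoL difference in change: 20 − 10 = 10 points (section 2.11).
- 50 per arm at baseline less 20% drop-out: 50 × 0.80 = 40 evaluable per arm (section 2.11).
- Standard deviation of the change: not stated, so back-solved below. This is an assumption.

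**Step 1. The plan's own figure.** Without an SD, 50 per arm cannot be reproduced from the stated inputs alone, but it is attainable. With n = 2(1.96 + 0.84)² × SD² / 10² and SD 15.9, n = 2 × 7.85 × 252.8 / 100 ≈ 39.7, so 40 evaluable and 40 / 0.80 = 50 enrolled. The number fits a continuous comparison.

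**Step 2. The standardised difference that 80% power implies.** With 40 per arm, a two-sample t-test at two-sided 5% has 80% power when d = 0.634, that is SD ≈ 10 / 0.634 ≈ 15.8. The normal approximation gives d = 0.626 and SD 15.96.

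**Step 3. Cut the same variable.** Assume normal scores with a common SD, the arms d apart, and one boundary c (in SD units from the midpoint). Then p(QDP) = Φ(d/2 − c) and p(CDC) = Φ(−d/2 − c), with c set to give the pooled share counted as high.

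Median cut (c = 0): Φ(0.317) = 0.624 against 0.376. The odds ratio is (0.624/0.376)² ≈ 2.8.
- Hand check by normal approximation: (0.248 − 1.96 × √(2 × 0.25/40)) / √(2 × 0.624 × 0.376/40) = (0.248 − 0.219)/0.108 ≈ 0.27, and Φ(0.27) ≈ 0.60.
- Exact enumeration of all 2×2 tables with 40 per arm: 63.5%.

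Exact results by pooled share counted as high, with d = 0.634. A share and its complement give the same power.

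| Share high | QDP v CDC | Power, score test | Power, Wald test |
|---|---|---|---|
| 50% | 0.624 v 0.376 | 63.5% | 63.5% |
| 33% | 0.442 v 0.218 | 57.1% | 57.0% |
| 25% | 0.348 v 0.152 | 53.2% | 51.8% |
| 15% | 0.220 v 0.080 | 43.9% | 32.6% |

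Section 2.12 names the Wald test, which does worse at extreme cuts. With d = 0.626 and the normal approximation throughout, the figures are 59.8% at the median and 51.3% at 25%, so the conclusion does not depend on the method.

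**Step 4. Sample size needed to recover the loss.** A median cut has large-sample efficiency 2/π ≈ 0.64 relative to the mean. Matching 40 continuous observations per arm takes 40 × π/2 ≈ 63 evaluable per arm, or 63 / 0.80 ≈ 79 enrolled. The normal approximation gives 64 evaluable (80 enrolled) at the median and 78 evaluable (98 enrolled) at a 25% or 75% cut.

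**Step 5. Diet quality.** The article gives no expected effect or SD for pHDI or nHDI, so no power figure can be computed.

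**The case against.** The strongest reply is that the plan does not replace the continuous analysis. Section 2.12 tests QoL scores, diet quality scores and six-month changes as continuous variables first, so a null odds ratio would stand beside another test. That is correct, and it limits the point to which effect estimate is promised. It does not remove it: the continuous route names p-values only, and its parametric test is for dependent samples, which does not compare arms (a separate matter).

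Several stronger readings are tempting and are not supported:
- *The plan claims 80% power for the odds ratios.* It does not. Section 2.11 ties 80% to the change in overall QoL and BMI. The comparison here is with the same effect left continuous.
- *The planned difference can never be obtained.* Too strong. Per-group means with 95% CI are planned for normally distributed variables, so a difference could be derived. It is just not named, with an interval, as an estimate.
- *The missing boundaries are an error, or will be picked from the data.* An article may leave category limits to a fuller document or to the questionnaire manual. Nothing says that several cuts will be tried and the best kept, so no inflated type I error can be charged to the plan.
- *High QoL contradicts the scale direction.* It plainly means good quality of life. Section 2.11 treats a fall in points as improvement.
- *The power loss applies equally to diet quality.* It cannot be quantified there.

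Two caveats on the QoL figure also stand. The back-solved d belongs to a change, whereas high QoL may be a status at six months with a different SD. And if overall QoL means ThyPRO's single overall item, with its five response categories, the normal model fits poorly.

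**Conclusion.** The concern stands in a limited form. The trial is sized on a continuous between-arm difference in change. The only comparative effect measure with an interval, and the only adjusted model, is an odds ratio, which for QoL and diet quality rests on scores cut into high or not. That choice is stated in the article and does not depend on what an unseen analysis plan may add about boundaries.

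For QoL, power falls from 80% to about 63% at best and to about 52–53% with 25% or 75% counted as high, with lower values for more extreme cuts. This rests on 40 evaluable per arm, d back-solved from the stated 80%, a normal shift, and the cut being made on the variable that was sized. For diet quality the point is loss of information only. The fault weakens interpretation but does not invalidate the trial, and it should be corrected.

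**What to change.** In section 2.12:
- For each continuous outcome, name the QDP-minus-CDC difference in six-month change with its 95% CI as the main estimate. Where a rank test is used, give a Hodges–Lehmann shift with CI.
- Put any covariate adjustment in a linear model of the continuous score.
- Keep the QoL and diet-quality odds ratios only as secondary or descriptive results, with cut-offs fixed before the data are seen.

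Odds ratios for outcomes whose boundaries the article already states (adherence, adiposity, metabolic markers) need no new definition.

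This changes analysis wording only, with no new data and no change to how the trial is run. The small downside is that the odds ratios, which some readers find easier to communicate, lose prominence.

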**Exclusion Criteria**: non-Hashimoto thyroiditis; pregnant or breastfeeding women; current/past use of dietary supplements, e.g., selenium or iodine; current use of other supplements in an amount above an upper level; diagnosed presence of other comorbidities: other endocrinopathy and metabolic diseases (e.g., diabetes, cardiovascular diseases), other thyroid diseases with chronic inflammation, diseases requiring an elimination diet (e.g., celiac disease, non-celiac gluten sensitivity, food allergy, food intolerance, etc.); other special diet with or without disease diagnosis lasting >4 months within the last 12 months: rigorous elimination diet (e.g., gluten-free, lactose-free), unbalanced diet (e.g., high protein, ketogenic), low-energy diet with an energy restriction >1000 kcal/day, very low-energy diet (e.g., liquid meal replacements), so-called ‘the autoimmune protocol’ and others that significantly change metabolism; underweight (BMI <18.5 kg/m^2^) or obesity with BMI ≥35 kg/m^2^; weight loss >4 kg in the last month.

**Table 3 ijerph-16-04841-t003:** The qualitative dietary protocol: (A) Self-monitoring diary for recommended foods.

Foods Recommended for Consumption Control the Frequency of the Food Consumption Every Meal/Eating Episode (or at least Every Day) and Check Adherence to Recommendations. Minimum Frequencies Are Indicated.							
Day	Vegetables (see diary B)	Foods rich in calcium e.g., milk, fermented milk drinks, curd cheese, cheese	Fruit	Whole grains e.g., buckwheat grain, wholemeal wheat and rye bread	Animal foods rich in zinc e.g., meats: beef, lamb, pork; eggs	Animal foods rich in selenium e.g., fish, seafood	Nuts and seeds e.g., nuts, pumpkin seeds, sunflower seeds
	Several times a day	Several times a day	Once a day	Once a day	Several times a week	Several times a week	Several times a week
Month: **Mark** ✕ **each time after food consumption**							
1							
2							
3							
…							
31							
*Month: June 2019 **Sample record of the Patient***							
*1*	✕✕	✕	✕✕	✕		✕	
*2*	✕✕✕	✕	✕	✕	✕	✕	
*3*	✕	✕✕✕	✕	✕		✕	
*4*	✕	✕✕		✕	✕	✕	
*5*	✕✕✕	✕	✕	✕	✕	✕	
*6*	✕✕	✕✕				✕	
*7*	✕✕✕	✕✕	✕		✕		

**Table 4 ijerph-16-04841-t004:** The qualitative dietary protocol: (B) Self-monitoring diary for foods with limited consumption.

Foods with Limited Consumption Control the Frequency of the Food Consumption Every Meal/Eating Episode (or at least Every Day) and Check Adherence to Recommendations. Maximum Frequencies Are Indicated.						

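### The logistic models analyse category status without naming the outcome visit or the T1 value of the same measure; the crude arm comparison is valid but gives away power that data already collected could partly recover.

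*Protocol article*

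**What the plan says.** For categorical outcomes, section 2.12 of the protocol article states that "logistic regression modeling will be applied to determine the chance of the occurrence of high diet quality, high AdhS, high QoL", and continues with low adiposity and elevated metabolic parameters. On covariates it says only: "A crude model and models with an adjustment for confounders will be created". Odds ratios are tested with Wald statistics. The sentence names no visit, and no covariate is listed. For continuous outcomes the same section works with the six-month change from baseline.

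Three other places matter:
- **Table 2** excludes "underweight (BMI <18.5 kg/m^2^) or obesity with BMI ≥35 kg/m^2", so BMI at entry runs from 18.5 to below 35. The cut-offs in section 2.9 (25 and 30) lie inside that range.
- **Table 1** schedules diet quality, quality of life, adiposity and metabolic parameters at T1, and again at T2 (one month) and T3 (six months).
- **Section 2.3** stratifies the randomisation by age only.

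**The concern.** A woman with BMI below 25 at entry who stays there counts the same as one who moved there during counselling. A woman well above the cut-off may lose weight as hoped and never cross it. When the outcome is a state, much of its variation was therefore already present at T1. A model without the T1 value treats that variation as noise, although it could be explained with data in hand.

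At stake are the precision and power of every between-arm odds ratio with a measured baseline. Stratifying by age alone also does nothing to balance the baseline state between arms of about 40 completers. Because T2 and T3 both supply the measures, it is not even fixed which visit the odds ratio describes.

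**Working it through.** **1. The plan's own sample size.** Inputs from sections 2.11 and 2.12: "a 5% significance level and 80% power were considered"; "two-tailed tests will be applied"; "in the experimental/control group, a decrease by 20/10 points and 2.0/1.0 kg/m^2^, respectively"; "50/50 for overall QoL and 42/42 for BMI", including 20% drop-out. No SD is stated, so it has to be solved from n:

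SD = difference / [(1.960 + 0.842) × √(2/n)]

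- QoL: 50 × 0.8 = 40 completers per arm, so SD = 10 / (2.802 × √(2/40)) = 16.0 points.
- BMI: 42 × 0.8 = 33.6, so 33 to 34 completers per arm, and SD = 1.45 to 1.47 kg/m².
- At 40 completers per arm, the BMI difference of 1.0 has 80% power with SD = 1 / (2.802 × √(2/40)) = 1.60 kg/m².

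The figures are coherent, but this is back-solving and not an independent check.

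**2. How far six-month status repeats entry status.** Assumptions not in the documents: normal entry BMI truncated to 18.5 to 35, mean 25 to 29, SD 3.5 or 4.5; low adiposity read as BMI <25. From the plan: mean decrease 2.0 v 1.0. Large simulated populations with SD of change 1.6 give (in %):

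| Entry mean / SD | Low at entry | Low at 6 months, QDP / CDC | Same category | Of those low at 6 months, already low | Crude power, 40 per arm |
|---|---|---|---|---|---|
| 25 / 3.5 | 48.5 | 69.0 / 59.1 | 80.7 | 72.8 | 14.8 |
| 25 / 4.5 | 46.6 | 64.4 / 55.7 | 83.4 | 75.0 | 12.2 |
| 27 / 3.5 | 28.1 | 50.0 / 39.8 | 80.4 | 59.5 | 14.8 |
| 27 / 4.5 | 32.0 | 50.3 / 41.5 | 83.5 | 66.9 | 11.9 |
| 29 / 3.5 | 13.1 | 31.4 / 22.6 | 84.5 | 45.5 | 14.0 |
| 29 / 4.5 | 19.7 | 36.4 / 28.2 | 85.4 | 57.9 | 11.9 |

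With SD of change 1.47, the same-category share is 80.9 to 85.9% and crude power 12.0 to 15.5%.

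Hand check of the third row: difference 0.500 − 0.398 = 0.102; SE = √(0.500×0.500/40 + 0.398×0.602/40) = 0.111; power ≈ Φ(0.102/0.111 − 1.96) ≈ 0.15.

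**3. What the T1 value adds.** 1,500 simulated trials per scenario, 40 per arm, SD of change 1.6, two-sided 5% Wald tests for the logistic models (power in %):

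| Entry mean / SD | Crude logistic | + T1 category | + T1 BMI, continuous | ANCOVA on continuous BMI |
|---|---|---|---|---|
| 25 / 3.5 | 15.0 | 21.6 | 27.9 | 78.3 |
| 25 / 4.5 | 13.5 | 17.9 | 23.3 | 79.9 |
| 27 / 3.5 | 16.3 | 19.5 | 29.3 | 77.9 |
| 27 / 4.5 | 13.6 | 17.4 | 24.3 | 79.7 |

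The continuous T1 value adds 10 to 13 points. The gap that remains to the continuous analysis is 49 to 57 points, and that is the cost of dichotomising.

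The median odds ratio is 1.46 to 1.56 crude and 3.30 to 3.39 given T1 BMI. These are different quantities (marginal and conditional), so the larger one is not a correction of the smaller.

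**4. Validity.** With a decrease of 1.0 in both arms (entry 27 / 4.5), type I error was 5.3% crude, 3.0% with T1 category, 3.5% with T1 BMI and 5.0% for ANCOVA. The simulation error at 5% is √(0.05×0.95/1,500) = 0.6 points.

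**The case against.** **The covariate list is open.** The article does not say that the adjusted models leave baseline out. A reader might infer that they do, because under randomisation the baseline value is prognostic and not strictly a confounder. On that strict reading no T1 variable would qualify, so the authors probably use the word loosely, and the list may stand in a fuller document. This stands: exclusion cannot be asserted. What remains is that the crude model has no baseline term by construction, and that the stated rule for the others does not call for one.

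**The visit is inferred.** This stands in part. The section's purpose is to assess the effect of counselling, so the outcome must come after T1, but the text does not choose between T2 and T3.

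**The crude comparison is not biased.** This stands. A reader might infer that chance baseline imbalance dominates the crude odds ratio. In one illustrative case (entry BMI about 26, SD 4) the imbalance has an SD of √(2×0.388×0.612/40) = 10.9 points, against a true difference of 9.7. But the ordinary SE of the six-month difference, √(0.59×0.41/40 + 0.49×0.51/40), is 11.1 points. The confidence interval already allows for such imbalance.

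**The gain is modest, and these are not the analyses the trial was sized on.** Both stand. Section 2.11 sizes on mean decreases, and section 2.12 analyses those measures as changes from baseline. A likelihood-ratio test reached 38% power in the illustrative case, but with 6.0% type I error, and it is not the planned test.

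**AdhS has no baseline.** This stands. It comes from diaries kept during follow-up, in the experimental group only.

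**Conclusion.** The point holds as one of efficiency and specification, not of validity. As written, the logistic models fix neither the outcome visit nor the T1 value of the same measure, though the data are collected and the entry range straddles the BMI cut-offs. Under the plan's BMI effect with 40 completers per arm and an assumed mean entry BMI of 25 to 27, 80 to 84% of women are in the same BMI <25 category at both times (about 85 to 86% at a mean of 29). Power is about 12 to 16% crude and 23 to 29% with continuous T1 BMI.

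A reader might go further and say that six-month status mostly repeats entry status for all these outcomes. The documents do not support that. They give no entry distribution. At an assumed mean BMI of 29, the share of women low at six months who were already low is 46 to 59%, so it can fall below half. Nothing was computed here for metabolic parameters, quality of life or diet quality, and Table 2 excludes diagnosed diabetes and cardiovascular disease, which may lower the share with elevated values at entry. Nor should the low power be blamed mainly on the missing baseline: dichotomising accounts for most of it.

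**What to change.** In section 2.12:
- State that the logistic outcomes are the categories at T3 (six months).
- For each outcome with a measured baseline, make the main logistic model contain arm, the T1 value of the same measure on its continuous scale, and age (the stratification factor).
- Restrict any further covariates to variables measured at T1.
- Label the crude model descriptive.
- Leave AdhS out of this rule.

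The cost is wording only, since Table 1 already schedules every T1 value needed. The downside is one of interpretation: the odds ratio is then conditional on baseline, is expected to lie further from 1 than the crude one, and must be reported as conditional. With T1 BMI in the model the Wald test was also slightly conservative in simulation (3.5%). The change does not restore the power lost by dichotomising.
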